**Fig. 3 Fig3:**
[figure not shown]
PAPMed trial Schedule of Procedures

### Analysis plan

The principle of intention-to-treat will be adopted in our analysis, where we will analyze clusters and patients as they have been randomized, regardless of the intervention they have received [50]. Individual patient data will be grouped by cluster and condensed to cluster level data. Summary analyses will be performed on a cluster level. Categorical variables will be reported as counts and proportions. Continuous variables will be reported as mean and standard deviation if symmetric or median with 25th and 75th percentile if skewed. Variables between the intervention and the control group will be compared, with *t*-test performed on continuous data and *χ*^2^ test performed on categorical data, and *P* value less than 0.05 is considered as statistically significant.

Effectiveness of the intervention on primary and secondary outcomes will be estimated with marginal modeling using generalized estimating equations (GEEs) to account for stratification and clustering [51, 52]. Robust variance estimation will be used to provide valid standard errors and to account for potential model misspecification [53, 54]. The modified Poisson approach with a log link will be used to obtain risk ratios for estimates of intervention effect with binary outcomes [53]. Main analyses will include adjustments for stratification and cluster effect. Baseline covariates will be cross-tabulated by randomization arm to check for substantial imbalance by chance. Additional analysis will be performed that will additionally adjust for identified imbalance baseline covariates. Potential effect measure modifiers impacting the effectiveness of the intervention program will be evaluated by stratified analysis. Imputation for missing data is not planned in main analyses since there is no reason to assume data is not missing at random. However, if we identify baseline covariates that are predictive of missingness, we will adjust for these covariates in additional analysis or implement multilevel multiple imputations to test for sensitivity of missing data on the results. For each outcome, we plan to report the estimate of intervention effect and its 95% confidence interval (CI), as well as estimate of intra-cluster correlation coefficients (ICCs) and its 95% CI.

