### Objectives

Our hypothesis is that the PAPMed intervention, compared to usual practices, can increase policy registration, save patient medication costs, and improve medication adherence and health outcomes. The primary objective of this study is to determine if the intervention program is superior to usual practices in promoting registration rate of rural patients in local governmental policy on outpatient reimbursement of chronic disease medicines. The secondary objectives are to determine if the intervention program is effective in reducing medication costs, increasing medication adherence, and improving health outcomes measured by blood pressure and blood glucose levels.

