### Study site

This study is being conducted in Tongzhou District, which is a district with high NCDs burden. According to a health census report based on medical examination data of regional health records of 125,769 participants aged over 65, the overall prevalence of hypertension and type 2 diabetes were 53.8% and 12.1%, while the control rates were 41.0% and 47.0%, respectively in 2017 [35]. Despite rapid urbanization in the past decade, a large socioeconomic gap remains between rural and urban residents of the district. In 2019, the annual disposable income of rural residents was 25,846 RMB (about 4011 United States Dollars (USD)), less than half of that of urban residents in Tongzhou district [36].

Tongzhou transferred from a rural county to an urban district in 2009 with a large proportion of the residents remaining rural. Rural areas are consisted of 12 townships, with 205 villages under these townships [37]. Two townships were selected to take part in this study based on the selection criteria of having (i) a typical representation of the socioeconomic development of rural areas of Tongzhou District, (ii) with village clinics serving 400 NCDs patients or more per year; (iii) available village doctors who can be trained to implement the intervention, and (iv) support from local healthcare institutions and township leaders. Majority of the residents in these two townships are under rural *hukou* (Chinese household registration system).

The local healthcare infrastructure is consistent with the primary healthcare system of rural China, characterized by a hierarchical system of county hospitals, district health centers (DHCs), THCs, and village clinics [38]. DHCs are secondary-level hospitals responsible for diagnosing and treating NCDs patients. There is one village clinic in each village with 3 to 7 village doctors carrying out regular quarterly follow-up visits on NCDs patients under the NEPHS program, mainly including monitoring blood pressure and blood glucose, health education, and medication consultation.

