### Outcome measurements

The primary outcome of the trial is the policy registration rate of NCDs patients recorded in CDMS. Information of NCDs patients registered in the policy will be collected and matched with CDMS at baseline, 3-month, and 6-month follow-up. Policy registration rate will be calculated as the proportion of NCDs patients registered in the policy in CDMS. The effectiveness of the intervention program will be evaluated by the policy registration rate between the intervention and the control arm. Secondary outcomes include the following:Total number of policy registrations including those that are not recorded in the hospital information system, collected at baseline and 6-month follow-up;Total hypertension and diabetes medication costs during duration of follow-up, collected at 6-month follow-up;Frequency of village doctor visits during duration of follow-up, collected at 6-month follow-up;Blood pressure level, including systolic blood pressure and diastolic blood pressure, measured with blood pressure monitor, if available from electronic health records or government-funded annual physical examination records;Blood glucose level, measured by blood tests, if available.

Data collection will rely on existing real-world administrative data (mainly insurance claims data) to reduce cost and increase study feasibility.

After the end of the follow-up period, we will also collect qualitative data through in-depth individual interviews of about six village doctors, ten patients, and several government officials and policymakers. Such data will provide insight on intervention fidelity, differential effects from different intervention components, and other feedback. We will conduct post-trial assessments relying on data collection from real-world administrative data periodically, to evaluate the longer-term effects of the intervention program. We will attempt dissemination of effectiveness of the intervention program through various channels, including policy forums or other forms with local healthcare officials. The trial schedule of procedures from beginning to end is shown in Fig. 3 below.

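### The main models for blood pressure and glucose leave out any pre-randomization reading and admit it only if imbalance is seen, which costs precision on the secondary health objective

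*Protocol article*

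**What the plan says.** The Objectives section of the protocol article makes "improving health outcomes measured by blood pressure and blood glucose levels" part of the secondary objectives.

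The Analysis plan covers all outcomes with one approach: "Effectiveness of the intervention on primary and secondary outcomes will be estimated with marginal modeling using generalized estimating equations (GEEs". Its covariate rule is "Main analyses will include adjustments for stratification and cluster effect". Baseline covariates are tabulated by arm, and then: "Additional analysis will be performed that will additionally adjust for identified imbalance baseline covariates".

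Under Outcome measurements, the registration outcomes have stated baseline collections. Blood pressure and glucose have no stated time point. Blood pressure is taken "if available from electronic health records or government-funded annual physical examination records". The glucose entry reads only "Blood glucose level, measured by blood tests, if available".

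The Study site section describes the doctors at each village clinic as "carrying out regular quarterly follow-up visits on NCDs patients under the NEPHS program, mainly including monitoring blood pressure and blood glucose".

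**The concern.** An earlier reading of the same quantity is usually the best available predictor of a later one. If it is dated before randomization, allocation cannot have affected it. With 15 villages per arm, village-to-village variation dominates the standard error for a continuous outcome, so explaining part of that variation is worth having.

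The plan does not leave this open. It states a rule that keeps the earlier reading out of the main estimate. The reading may enter a further analysis, but only after the arms have been inspected for imbalance. That has two consequences:

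- The main confidence interval is wider than the data may allow.
- Whether an adjusted result exists at all depends on what the baseline table happens to show.

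The outcomes at stake are the two that carry the secondary health objective.

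**Working it through.** **The plan's own figure.** The Statistical power section covers registration only: 15 villages per arm, 5250 patients (read as per arm, so 5250/15 = 350 per village), ICC 0.04, and an 8.5-point difference. The design effect is 1 + 349 × 0.04 = 14.96, and the effective sample is 5250/14.96 = 351 per arm. Power (pooled z) is 89.8% from a control rate of 10%, 94.7% from 7% and 97.4% from 5%. The claim of more than 90% at a rate below 10% therefore reproduces. The article gives no SD, ICC, target effect or power for blood pressure or glucose.

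**Assumptions for systolic pressure.** SD 18 mmHg, 350 patients per village, ICC 0.02 to 0.05, and a correlation r of 0.5 to 0.7 between the pre-trial and later reading at both patient and village level. None of these is in the article except the patient count.

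**Main model as written.** SE = 18 × √(2 × (1 + 349 × ICC)/5250).

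- ICC 0.02: 18 × √(2 × 7.98/5250) = 0.99 mmHg
- ICC 0.04: 18 × √(2 × 14.96/5250) = 1.36 mmHg
- ICC 0.05: 18 × √(2 × 18.45/5250) = 1.51 mmHg

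Reading 5250 as the trial total (175 per village, 2625 per arm) changes little: 18 × √(2 × 4.48/2625) = 1.05 and 18 × √(2 × 9.70/2625) = 1.55 mmHg at ICC 0.02 and 0.05.

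**With a pre-randomization reading.** SE × √(1 − r²).

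| r | Factor | SE at ICC 0.02 | SE at ICC 0.05 | Reduction |
|---|---|---|---|---|
| 0.5 | √0.75 = 0.866 | 0.86 | 1.31 | 13% |
| 0.7 | √0.51 = 0.714 | 0.71 | 1.08 | 29% |

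**If only the village mean is used.** The variance of a village mean is proportional to ICC + (1 − ICC)/350. At ICC 0.04 this is 0.0400 + 0.0027, so about 94% lies between villages. A village-level correlation of 0.5 gives √(1 − 0.94 × 0.25) = 0.87, and 0.7 gives √(1 − 0.94 × 0.49) = 0.73. Most of the gain is kept.

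**What could be detected.** Thirty villages less two arms and one township term leave 27 degrees of freedom, so the effect detectable with 80% power is about (2.05 + 0.86) × SE = 2.91 × SE. At ICC 0.04 it is 2.91 × 1.36 = 4.0 mmHg unadjusted. Adjusted, it is 2.91 × 1.18 = 3.4 mmHg at r = 0.5 and 2.91 × 0.97 = 2.8 mmHg at r = 0.7. Even the smallest SE in the table gives 2.91 × 0.71 = 2.1 mmHg.

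**What arm difference might arise.** Suppose each extra registrant gains 5 mmHg. The 8.5-point design difference then gives 0.085 × 5 = 0.43 mmHg, below every SE above. The pilot village went from 17 to 148 registrations. Those 131 extra, out of an assumed 350 to 400 patients, are 33% to 37%, and at 35% the arm difference is 0.35 × 5 = 1.75 mmHg, above every unadjusted SE.

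**Glucose, illustration only.** With an assumed SD of 2.0 mmol/L, ICC 0.04 and 70 patients per village, SE = √((2/15) × (4 × 0.04 + 4 × 0.96/70)) = 0.17 mmol/L. With r = 0.5 it becomes 0.15.

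**The case against.** The strongest reply is that a stratification-adjusted main model with covariate-adjusted supporting analyses is a recognized, defensible choice. Villages are randomized within township and the GEE uses robust variance, so chance village differences are already in the confidence interval. Both outcomes are secondary and opportunistic, and extra parameters are not free with 30 clusters. All of this stands, and it limits the point to precision and prespecification.

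Some stronger readings are tempting, and the documents do not support them:

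- *Chance village differences exceed any plausible effect.* The article gives no SD, ICC or effect size for these outcomes. Under the assumptions above the statement is true at the 8.5-point difference but fails at pilot-like uptake, where 1.75 mmHg exceeds an SE of 0.99 to 1.51. The 8.5 points is also a detectable difference, not a forecast of uptake.
- *Routine records certainly hold a pre-trial reading.* Quarterly monitoring makes this likely, but the article does not say that those readings sit in the records used for outcomes. Blood pressure is subject to availability, and no record source is named for glucose.
- *The outcomes are compared at follow-up only.* The text gives no time point. Fig. 3, which was not visible in the text reviewed, may give one.

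A further reply is that covariates for secondary outcomes can wait for a statistical analysis plan. That would answer silence. Here the article states the rule for its main analyses, and neither an unseen schedule nor an unseen plan removes it.

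**Conclusion.** The point holds as a matter of efficiency and prespecification. For systolic pressure, leaving out the pre-randomization reading forgoes a reduction of about 13% to 29% in a standard error of about 1.0 to 1.5 mmHg. This rests on an assumed SD of 18 mmHg, 350 patients per village, ICC 0.02 to 0.05 and baseline correlation 0.5 to 0.7. The glucose figures are illustrative only.

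A reader might infer that the unadjusted comparison is biased, or that chance imbalance could pass for a treatment effect in some way the interval misses. Neither follows: the randomized comparison is unbiased and the robust standard error reflects village variation. Nor does adjustment rescue very small effects, since arm differences below about 1 mmHg stay out of reach in every case worked here. The conclusion on registration rate does not change.

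**What to change.** In the Analysis plan, prespecify for systolic pressure, diastolic pressure and glucose that, where pre-randomization readings are available, the main model includes the last value dated before randomization, regardless of observed imbalance:

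- If the data are condensed to village level, as that section describes, use the village mean of those values.
- If patient-level data are modelled, use the patient's value with a missing indicator, so that patients without an earlier reading are kept.

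In Outcome measurements, state the look-back window for the pre-randomization value. Keep the stratification-only model as a sensitivity analysis.

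The cost is an earlier date range in the record extraction and one to three extra model terms. With 30 clusters the terms should be few, and the village mean alone keeps most of the gain. No new measurement and no contact with control villages is needed. If the records turn out to hold too few earlier readings for an outcome, the present main model stands for that outcome, and the report should say so.

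### Presuming data missing at random is no reason to skip imputation when the main analysis is an unweighted GEE; blood pressure and glucose are the outcomes exposed

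*Protocol article*

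**What the plan says.** All the analysis statements are in the Analysis plan section of the protocol article.

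- Missing-data rule: "Imputation for missing data is not planned in main analyses since there is no reason to assume data is not missing at random".
- Estimator: effects on primary and secondary outcomes "will be estimated with marginal modeling using generalized estimating equations (GEEs) to account for stratification and clustering".
- Model content: "Main analyses will include adjustments for stratification and cluster effect". Baseline covariates enter only in an additional analysis, and only if found to be imbalanced.
- Standard errors: "Robust variance estimation will be used to provide valid standard errors and to account for potential model misspecification".
- Fallback: "if we identify baseline covariates that are predictive of missingness, we will adjust for these covariates in additional analysis", or multilevel multiple imputation will be run as a sensitivity check.

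Under Outcome measurements, blood pressure is a secondary outcome used "if available from electronic health records or government-funded annual physical examination records". The entry for glucose reads "Blood glucose level, measured by blood tests, if available".

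**The concern.** The rule takes data to be missing at random and concludes that imputation is unnecessary. That inference can be defended for a likelihood-based model that contains the variables driving missingness. It does not carry over to an unweighted GEE. A GEE fitted to whatever values were recorded is generally valid only if values are missing completely at random, or if missingness depends only on covariates in the model. Here the model holds arm and township. If recording also depends on, say, age or earlier blood pressure, the data are still missing at random given those variables, but the main estimate can be biased. Robust variance estimation corrects standard errors; it does not remove bias caused by which patients were measured. Condensing the data to village level does not help either, because a village mean of available values carries the same selection.

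At stake are the estimates for blood pressure and glucose, which the Objectives section makes part of a secondary objective. They would come from an analysis that the plan's own stated assumption does not support.

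**Working it through.** The protocol states no missingness rate and no missing-data figure, so there is nothing of its own to reproduce on this point. The statement on power concerns registration and does not bear on it.

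**1. Assumption set against estimator**

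| Element | Protocol | What it needs or gives |
|---|---|---|
| Presumed mechanism | Missing at random | Makes multiple imputation valid, given the right variables |
| Main estimator | GEE, no imputation, no weighting described | Missing completely at random, or missingness explained by model covariates |
| Covariates in main model | Arm, township | No patient-level predictor of outcome |
| Fallback | Conditional, additional or sensitivity analysis | Main estimate unchanged even if predictors of missingness are found |

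The mechanism in the first row does not license the estimator in the second.

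**2. Could recording differ by arm?** Under Follow-up, intervention village doctors must see all registered patients in months 1, 3 and 6 and monitor blood pressure and glucose. Under Control, the other villages continue usual practice, which the Study site section describes as quarterly visits that also monitor both. Differential recording is therefore plausible, but it is an inference; no section says it will occur.

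**3. Hand calculation (all inputs assumed).** The mean among measured patients in an arm is the sum of (share × proportion measured × group mean) divided by the sum of (share × proportion measured). Take two equal groups with mean systolic pressure 150 and 135 mmHg, and no treatment effect.

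- True mean: 0.5 × 150 + 0.5 × 135 = 142.5.
- Control arm, 60% and 40% measured: (0.5 × 0.6 × 150 + 0.5 × 0.4 × 135) / (0.5 × 0.6 + 0.5 × 0.4) = 72 / 0.5 = 144.0.
- Intervention arm measured evenly: 142.5. Spurious difference: 142.5 − 144.0 = −1.5 mmHg, an apparent benefit.
- Intervention arm measured 60% and 40% as well: 144.0 − 144.0 = 0.

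**4. Simulation (all inputs assumed).** 30 villages of 100 patients; systolic pressure = 140 + effect × arm + 9x + village term (SD 3) + residual (SD 11), where x is a standardised, fully observed baseline covariate. The log-odds of being measured are 0.8 + 0.7x, with the x term either in the intervention arm only or in both arms. About 31 to 33% of values are missing in each arm. The model is a GEE with independence working correlation, adjusted for arm and township; 150 replicates; Monte Carlo standard error about 0.1 mmHg for the available-data estimate.

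| Missingness depends on x | Full data | Available data, arm and township | Available data, x added |
|---|---|---|---|
| Intervention arm only, no effect | 0.00 | +1.84 | 0.02 |
| Intervention arm only, effect −3 | −3.06 | −1.20 | −3.06 |
| Both arms alike, effect −3 | −3.00 | −3.03 | −3.00 |

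The shift of 1.84 is the slope of 9 times a mean x of about 0.20 among measured intervention patients (1.84 / 9 = 0.20). Here the bias works against the intervention; in step 3 it favours it. Neither direction can be predicted from the protocol.

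The same mechanism affects a risk ratio from the modified Poisson model. For a generic binary outcome with arm-dependent missingness, 1.86 on full data becomes 2.00 on available data and returns to 1.86 once x is added. With the same pattern in both arms it is 1.86 against 1.85.

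**The case against.** The authors may have meant that they see no sign of systematic missingness, that is, missing completely at random. The next sentence then reads sensibly: presume it, check baseline predictors, act if the check fails. The fallback is prespecified, its trigger is predictors of missingness rather than treatment results, and it already offers to "we will adjust for these covariates in additional analysis or implement multilevel multiple imputations to test for sensitivity of missing data on the results". On that reading the repair could be a single phrase. What remains is that the text does not say this, and that a failed check would still leave the main estimate as it was.

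It is also fair that the bias is conditional. Availability that differs only by arm is absorbed by the arm term. Bias in the contrast needs missingness to depend on a predictor of outcome differently in the two arms, and the simulation shows almost none otherwise.

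A reader might infer more than the documents support:

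- That the plan contradicts itself by using measurements only where available. It does not: this admits gaps without saying what causes them.
- That trial follow-up determines which values are recorded. Control villages also have routine quarterly monitoring, and intervention doctors are encouraged to merge trial visits into theirs.
- That the trial's main conclusion is at risk. Registration is a match of policy records to the chronic disease management system, where little missingness is expected.

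Detailed missing-data methods are commonly left to an analysis plan. That does not excuse a rationale the article itself states wrongly.

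**Conclusion.** The point stands as an error of justification with a consequence for two secondary outcomes. The stated reason does not support the stated analysis, and the conditional fallback does not change which estimate is the main one. The available-data estimate can be biased; it is not shown to be. Under the assumed inputs the size is from about zero to about 1.5 to 1.8 mmHg systolic, and the sign depends on who is measured in which arm. The upper end rests on roughly 31 to 33% missing in the simulation, or 40 to 60% measured in the two control groups of the hand calculation, together with a dependence on an outcome predictor that differs by arm. None of these figures comes from the protocol. No such bias is claimed for the primary outcome.

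**What to change.** 1. Delete the justification, or state the assumption the main GEE actually needs and defend it.
2. For blood pressure and glucose, make the main analysis a GEE adjusted for prespecified baseline predictors, including the patient's baseline value where recorded, with multilevel multiple imputation or inverse-probability weighting carried out by arm. Keep the available-data GEE with arm and township as the sensitivity analysis.
3. Report the proportion measured by arm for both outcomes.
4. Do not add a general statement that claims-based outcomes need no imputation. The protocol does not say that the patient list is fixed. It also reports that a substantial group of patients buys medicines at pharmacies, while the policy applies to designated public institutions, so claims may not capture all medication costs.

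The cost is wording and modest extra analysis, since multilevel imputation is already named. The drawback is reliance on baseline values that may be incomplete for the same reasons as the outcomes; the protocol does not say that they exist for every patient, so the imputation model must allow for gaps in them.
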